**Fig. 3 Fig3:**
[figure not shown]
IBD-live schedule of enrollment, interventions, and assessments. Comparability between groups will be assessed by summarizing emotional maturity (Bar-On EQI:JV), quality of life (IMPACT-III), and drug adherence (Morisky Medication Adherence Scale, MMAS). All of these questionnaires will be completed at home within one week after enrollment

The outcome parameter of the economic evaluation is the number of relapses within one year. With this outcome parameter, the incremental cost-effectiveness ratio provides information to guide preference of the web-assisted calprotectin-based treatment algorithm over usual care. The time horizon of the evaluation will be from randomization to the end of the study. Uncertainty surrounding cost-effectiveness ratio will be explored by bootstrap replication and by varying the major cost components. Discounting will *not* be applied. The economic evaluation will be performed from a societal perspective, incorporating costs of travel to the hospital and costs of leave from work of the parents, as well as direct medical costs of IBD care (costs of medication, outpatient visits). Questionnaires will be used to collect data regarding health care consumption, travel and time costs and productivity loss at study entry and at one-month intervals thereafter. Other relevant data regarding health care consumption such as number of contacts or visits with the local IBD team, unscheduled health visits, hospital admissions, and drug use will be recorded or collected from existing hospital databases. Unit prices will be determined according to Dutch guidelines. Standard prices will be used if available and applicable, according to the type of hospital where the patient is treated. Productivity loss will be calculated using the friction cost method. The IMPACT-III score will be used in the patient outcome analysis and provides an estimate of the relationship between the difference in quality of life and the difference in costs of both treatments. At the end of the observation period we will evaluate the teenagers and caretakers in the intervention group for their attitude towards E-health.

### Other study parameters

Emotional maturity may be a risk factor for poor adherence and is therefore assessed at the start of the study using the Bar-On Emotional Quotient Inventory (Youth Version) [31]. Emotional maturity as well as the level of education of patients and parents are to be used as covariables in the final data analyses. Stool samples will also be tested for colon pathogens (*Salmonella enterica, Campylobacter jejuni*, Shigella spp/EIEC, *Giardia lamblia*, STEC) and parasites (*Cryptosporidium* spp, *Dientamoeba fragilis*, *Entamoebe histolytica*) with the real-time multiplex PCRs, to control for false positive fCal values [32, 33].

### Participant timeline

Teenagers who are potentially eligible based on inclusion criteria will be identified and informed about the trial by the local IBD team. In case the teenager is interested in participation an information pack will be sent by mail, containing a patient invitation letter, a participant information sheet and consent forms. Patients who do not participate due to exclusion criteria or refusal will be anonymously recorded, including patient characteristics and, if available, the reason for non-participation.

During the outpatient appointment the health provider will (1) recheck whether the participant has daily access to a smartphone or tablet or an internet connection, (2) assess whether the last relapse was more than three months before, and (3) identify parents or legal guardians. After written informed consent has been obtained, but before randomization occurs, each patient will undergo a detailed assessment (Fig. 3). Data collected will include demographic information (including travel time to clinic, level of education of both patient and parents), clinical and IBD-specific history (including age at diagnosis, type of IBD, disease location, date of last relapse and current maintenance treatment). The (pediatric) gastroenterologist will perform a general physical examination (including measurements of height and weight, and assessment of pubertal maturation) and will rate the current disease activity by using the PCDAI or PUCAI.

Irrespective of group assignment, each participant will be evaluated at the local trial site at six and twelve months for disease activity (by physician rated PUCAI or PCDAI), serological markers of inflammation and fCal. Each participant will complete a diary for school-absenteeism and parental absence from work once every month, and IMPACT-III and MMAS questionnaires at six and twelve months. Reminders will be sent by email, with a direct link to the online questionnaires.

In between scheduled health visits teenagers assigned to the experimental group receive alerts to use the online flarometer and to send a feces sample by pre stamped return envelope for fCal rapid analysis. Teenagers assigned to usual care may have outpatient appointments at three and nine months, depending on the health check interval prior to participation.

### Sample size

In earlier versions of the study protocol (v1 to v5) the primary outcome was defined as the number of relapses per group during a 52-week follow-up. The nul-hypothesis was based on a relapse rate of 40 % in the control group [34], whereas the alternative hypothesis stated that in the experimental group this percentage would drop down to 25 % [13]. We wished to detect this difference by a two-sided test at 5 % level of significance with a probability of 80 %. With the binary outcome (event or not) 152 patients per group were needed.

Accumulating data from the study as it continued allowed re-estimating the sample size. Adapting the primary outcome from ‘number of events’ to ‘time-to-event’ per group could reduce the required sample size. To detect a 15 % reduction in the absolute relapse risk after 52 weeks of follow-up with a two-sided significance level of 5 % and with 80 % power, we calculated that we need 90 patients per group (taking into account a maximum of 10 % loss-to-follow-up).

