**Methods/design:**

A randomized trial of web-based disease monitoring versus usual care is conducted at 10 Dutch IBD care centers. We plan to recruit 180 patients between 10- and 19-years old with quiescent IBD at baseline. Teenagers assigned to IBD-live will use the flarometer -an automatic cumulation of disease activity and fecal calprotectin measurements- to estimate probability of relapse. In case the flarometer indicates high risk the patient requires treatment intensification in accordance with national guidelines; low risk means that maintenance therapy is unchanged; and intermediate risk requires optimisation of drug adherence. Patients assigned to usual practice get the best accepted medical care with regular health checks. Primary outcome is the frequency of relapse at 52 weeks of follow-up. The diagnosis of relapse is based on a clinical activity index score >10 points necessitating remission induction therapy. Secondary outcomes include quality of life and cost-effectiveness.

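### The revised 90 per group does not follow from the only relapse rates printed (40% vs 25%); at those rates its power is about 53–59%, and the change to a time-to-event outcome cannot explain the fall from 152.

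*Protocol article*

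**What the plan says.** All of this is in the protocol article, mainly under Sample size.

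- For protocol versions 1 to 5 the hypothesis was "based on a relapse rate of 40 % in the control group", and "in the experimental group this percentage would drop down to 25" per cent. The test was two-sided at 5% with 80% power, and "With the binary outcome (event or not) 152 patients per group were needed".
- The section then says that accumulating data permitted a re-estimate, and that changing the outcome from number of events to time-to-event "per group could reduce the required sample size".
- The revised target is stated as "To detect a 15 % reduction in the absolute relapse risk after 52 weeks of follow-up". The two-sided 5% level and the 80% power are the same as before, and the result is "we calculated that we need 90 patients per group". That figure already allows for at most 10% loss to follow-up.
- No new control rate, hazard ratio or number of events is printed.
- Elsewhere, Outcomes specifies a two-sided log-rank test on time to relapse, Randomization and masking gives 1:1 allocation, and Retention gives 52 weeks of follow-up per patient.

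**The concern.** The effect size, significance level and power all appear unchanged between the two calculations, yet the requirement falls from 152 to 90 per group, a cut of 62/152 = 41%. The 90 includes a loss allowance and the 152 does not, so the like-for-like fall is larger still, to 90 × 0.9 = 81 evaluable. The only reason offered is the change of outcome type.

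With the same fixed follow-up for every patient, log-rank power depends on the number of relapses, and it is close to the power of a comparison of two proportions at 52 weeks. Such a change should save very little. If 40% vs 25% is still the planning hypothesis, the trial is well short of its stated power, and a null result could be given more weight against IBD-live than it deserves.

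**Working it through.** **Inputs.** From Sample size: control 40%, experimental 25%, two-sided 5%, 80% power, 10% loss. From the other sections: 1:1 allocation, 52-week follow-up, log-rank test. z-values are 1.960 and 0.842, so (1.960 + 0.842)² = 7.849. Assumption: proportional hazards.

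**1. The earlier figure.** Two proportions, pooled variance, mean rate 0.325:

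n = [1.960·√(2·0.325·0.675) + 0.842·√(0.40·0.60 + 0.25·0.75)]² / 0.15² = (1.298 + 0.550)² / 0.0225 = 151.9.

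This matches the printed 152, with no allowance for loss.

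**2. The same rates by log-rank test.**

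- Hazard ratio = ln(0.75)/ln(0.60) = 0.563; ln(HR) = −0.574.
- Schoenfeld events: 4 × 7.849 / 0.574² = 95.2.
- Freedman events: 7.849 × (1.563/0.437)² = 100.5.
- Expected events per pair of patients, one in each arm: 0.40 + 0.25 = 0.65.

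| | Schoenfeld | Freedman |
|---|---|---|
| Per group before loss | 95.2/0.65 = 146.5 | 100.5/0.65 = 154.6 |
| Per group with 10% loss (÷ 0.9) | 163 | 172 |

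Rounding events up to 96 and 101 gives 164 and 173. The saving from the change of outcome is (152 − 147)/152, about 3%, by Schoenfeld and nothing by Freedman.

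**3. Power of 90 per group at 40% vs 25%.** Schoenfeld power = Φ(√D·|ln HR|/2 − 1.960), with D the number of events.

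- 81 evaluable: D = 81 × 0.65 = 52.65; Φ(2.083 − 1.960) = 55%.
- 90 with no loss: D = 58.5; Φ(2.196 − 1.960) = 59%.

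| | Schoenfeld | Freedman | Two proportions | Simulated log-rank |
|---|---|---|---|---|
| 81 evaluable | 55% | 53% | 53% | 54% |
| 90, 10% dropping out during the year | – | – | – | 56% |
| 90, no loss | 59% | 57% | 58% | 58% |

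The simulation used 20,000 runs, exponential times and censoring at one year.

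**4. Which control rates would give 90?** A 15-point reduction, 81 evaluable per group, Schoenfeld:

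| Control vs experimental | Power |
|---|---|
| 50% vs 35% | 51% |
| 40% vs 25% | 55% |
| 35% vs 20% | 59% |
| 30% vs 15% | 66% |
| 25% vs 10% | 76% |
| 23.5% vs 8.5% | 80% |

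At 23.5% vs 8.5% the requirement is 80.5 per group, and 80.5/0.9 = 89.5, which agrees with the printed 90. By Freedman the control rate has to be about 20% or lower. At the other end, 80% returns only near 89% vs 74% and above.

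**5. Detectable difference.** With 81 evaluable per group and 40% in controls, a fall to 20.5% gives HR = ln(0.795)/ln(0.60) = 0.449. That needs 49.0 events by Schoenfeld, and 49.0/0.605 = 81 per group.

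**The case against.** The strongest reply is that 40% vs 25% belongs to versions 1 to 5. The revised sentence repeats only the 15-point reduction and follows a remark that accumulating data allowed re-estimation. Nothing says that 40% was kept, and 23.5% vs 8.5% reproduces 90 with the loss included. The article also condenses a full protocol that may give the updated rate, hazard ratio and event count. This stands in part. A reader might infer that the 80% power claim is simply false; the document does not support that, because the rates behind the 90 are not printed. Their absence alone would not be a finding.

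What the reply does not explain is the text as printed. Fifteen points is exactly 40 minus 25. The saving is credited to the outcome type and not to a new rate. The control rate required lies below the 25% that the earlier hypothesis assumed for the experimental arm.

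A reader might also infer a second shortfall from the abstract, which still says "Primary outcome is the frequency of relapse at 52 weeks of follow-up", since the article itself puts the binary requirement at 152. The document does not support that either. Outcomes fixes a log-rank comparison of time to relapse, so the leftover wording does not make a binary test primary.

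The statement that the change could reduce the sample size is literally true by Schoenfeld (152 to 147). The fault is the size of the saving credited to it. Finally, counting 81 evaluable discards follow-up that a log-rank test would partly use, so 55% is one value within a range.

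**Conclusion.** The concern holds in conditional form. The printed number does not follow from the only printed rates: about 163–173 per group would be needed with 10% loss, against 90. If 40% vs 25% still applies, power is 53–59% depending on the method and the handling of loss, so the chance of missing that effect is 41–47% and not 20%. The change of outcome cannot account for the reduction under any rate, because the two kinds of test need nearly the same number at 40% vs 25% when follow-up is fixed, and only a different control rate brings the requirement to 90. Whether such a rate was adopted cannot be told from the article. The figures assume proportional hazards, 1:1 allocation and 52 weeks of follow-up for all patients apart from losses.

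**What to change.** Rewrite the Sample size paragraph in one of two ways.

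1. If a different control rate was used, state that rate, the hazard ratio and the number of events that give 90, and credit the reduction to that rate.
2. If 40% vs 25% still holds, keep 90 per group but state power of about 55% (range 53–59%), and give the difference detectable with 80% power as about 40% vs 20.5% (Schoenfeld, 81 evaluable per group).

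In both cases, correct the statement that the time-to-event outcome is what reduces the sample size; at 40% vs 25% it accounts for about 3% at most.

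The cost is a change of wording and, in the second case, a less favourable stated power. No extra patients are needed.

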### Randomization and masking

Eligible patients for whom consent or assent is provided will be allocated in a 1:1 ratio to the two arms of the study according to a computer-generated random sequence stratified by research site and disease type (Crohn’s disease vs. ulcerative colitis), and using blocks of variable size. The allocation sequence is generated by the biostatistics unit of the UMCG, and is not available to any member of the research team. Allocation concealment will be ensured, as the study website (https://www.ibd-live.nl) will not release the randomization code until the teenager has been recruited into the trial, which takes place after all baseline measurements have been completed. The nature of the intervention does not allow blinding of participants, care providers, or outcome assessors.

### Retention

Once a teenager is randomized, the study site will make every reasonable effort to follow the patient for the entire study period of 52 weeks. It is projected that the rate of loss-to-follow-up will be at most 10 %. Retention will be promoted by sending automated reminders to the participants in the experimental study arm to use the flarometer, careful planning of outpatient appointments to avoid school calendar breaks, and facilitating stool collection with feces collection papers. Questionnaires will be completed digitally via a hyperlink sent by email, which will further limit participant burden.

There will be no explicit incentive for study participants. Participation in a child friendly website may be perceived as an incentive, but it is not an incentive in a material sense. Teenagers in the experimental arm will have access to the website, while the controls will only have access to the study questionnaires.

A participant who withdraws consent for follow-up assessment of any of the secondary outcomes will be given the option to continue with assessments for the primary outcome.

### Confidentiality and data management

Consecutive patients participating in the study will receive a unique study number. All data will be entered electronically and stored linked to this study number. Patients will complete digital questionnaires via a hyperlink sent by email, which will automatically be linked to the corresponding study number. Patients with access to the IBD-live website will use their username and password for identification/login. The username will be linked to the unique study number in order to store all data concerning flarometer results.

Local trial sites will have access to the flarometer data of their own patients only. The coordinating investigator in the UMCG and the webmaster are the sole persons who have access to the full subject identification code list in order to be able to link patient login-ID to the corresponding study number.

Feces samples will be marked with a study number label and sent to the Department of Laboratory Medicine at the UMCG. fCal results will be uploaded on the website by the coordinating investigator and will be visible to the individual patients and their local IBD team. After measurement of fCal levels the residual material will be analyzed for detection of microbial gut pathogens.

Data will be stored during the study period and until 15 years thereafter. When patients and their parents give permission, residual feces will be stored for a maximum period of 15 years for future diagnostic research.

### Statistical methods

The statistical analysis will be coordinated by a statistician from the biostatistics unit of the UMCG. The primary analyses will be conducted using an intention-to-treat basis. All teenagers recruited into the study will be included in these analyses; patients will be analyzed within the group (IBD-live or usual practice) to which they were randomized irrespective of what care they actually received. Where appropriate, secondary analyses will be conducted using a per protocol basis. These analyses will be restricted to just those teenagers who replied to more than 80 % of the alerts to use the flarometer and to the teenagers in the control group who replied to more than 80 % of the requests to send a stool sample for fCal measurement.

As earlier published web-based programs have focussed on patients with ulcerative colitis [17, 35, 36], we made an a priori decision to do a subgroup analysis to examine the intervention in two subtypes of IBD (ulcerative colitis and Crohn’s disease). We will use a test of interaction to examine whether the treatment effect differs between these subgroups. In case of random missing data multiple imputation will be performed using the hot deck method [37].

### Data monitoring

A Data Safety Monitoring Board (DSMB) has been established. The Chair of the DSMB is [name] (epidemiologist at the University Medical Centre Groningen), with [name] (statistician, UMCG), and [name] [name], paediatrician at Wilhelmina Hospital Assen). The Charter and responsibilities of the DSMB are available on request from the IBD-live study office. The DSMB is independent of the study organizers. During the period of recruitment to the study, one interim analysis will be supplied, in strict confidence, to the DSMB, together with any other analyses that the committee may request. In the light of this interim analysis, the DSMB will advise the trial steering committee if, in its view, the active intervention has been proved, beyond reasonable doubt, to be different from the control (usual practice) for all participants. The trial steering committee can then decide whether or not to modify intake to the trial. The advice of the DSMB will only be sent to the sponsor of the study. Should the sponsor decide not to fully implement the advice of the DSMB, the sponsor will then send the advice to the reviewing Medical Ethical Committee (MEC), including a note to substantiate why (part of) the advice of the DSMB will not be followed.

### Premature termination of the study

An interim safety analysis will be performed after the first 50 participants in both arms have completed the first six months of the study. The interim-analysis will be performed by the trial statistician. This will be based on the number of clinical relapses, a significant difference in IBD-associated hospital admissions and/or emergency visits and/or unscheduled health visits, to the detriment of the intervention group (IBD-live). As we expect a non-normal distribution, the Mann–Whitney *U* test will be used to test the differences that may have occurred. As it may be hard to show a statistically significant difference due to the sample size we propose a composite-core as proxy for severity of clinical deterioration of IBD during the study, based on objective parameters. In this score an unscheduled health visit = 1 point, an emergency visit = 2 points, and a hospital admission = 4 points. Given a sample size of n = 50, an α of 0.05 (two-tailed) and an estimated standard deviation of 4 points, we can reliably show a difference of 3 points on the composite-score, which equals one hospital admission.

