### Interventions—modifications

Study participants from both groups are instructed to contact their doctor immediately to report clinical deterioration between regular health checks, or if at any time they want a consultation (side effects, other health related questions). Rapid access to specialist care is guaranteed for both groups. All unscheduled health visits (including those at the IBD clinic, general physician and emergency department) and hospital admissions are documented in the study data tracking system and are reported as adverse events. Crosschecking will be done by comparing doctor reported health consumption and patient-reported health consumption.

Study participants can leave the study at any time for any reason if they wish to do so without any consequences. The local principal investigator can decide to withdraw a teenager from the study for urgent medical reasons. Another patient from the same center may then be randomized to enter the study.

Patients withdrawn from the experimental arm of the trial will continue with usual care, outside the scope of this study, as would have happened otherwise. Patients who receive usual care and withdraw from the study will continue to receive usual care as before entering the study.

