### Trial status

Recruitment began on 6 June 2013. It is anticipated that study recruitment will be completed by 30 September 2015, and that the trial will conclude by 30 September 2016.

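### The interim safety comparison is triggered by and sized on six-month completers with no stated analysis set; counting all randomized patients per person-time would be cheap and more sensitive

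*Protocol article*

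**What the plan says.** The Protocol article sets the trigger in its section on premature termination, where it states: "An interim safety analysis will be performed after the first 50 participants in both arms have completed the first six months of the study". The same section bases the look on relapses, admissions, emergency visits and unscheduled visits. It adds a composite score ("an unscheduled health visit = 1 point, an emergency visit = 2 points, and a hospital admission = 4 points") and names the Mann-Whitney test. Its precision statement takes these inputs: "Given a sample size of n = 50, an α of 0.05 (two-tailed) and an estimated standard deviation of 4 points". From them the authors draw the claim that "we can reliably show a difference of 3 points on the composite-score, which equals one hospital admission". The section also concedes that significance may be hard to reach at this sample size.

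Three other sections bear on the point:

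- **Interventions—modifications:** "The local principal investigator can decide to withdraw a teenager from the study for urgent medical reasons". The vacated place can be filled by a new patient at that center. Unscheduled visits and admissions are documented for both groups.
- **Statistical methods:** intention-to-treat is stated for the primary analyses. The interim is not mentioned.
- **Data monitoring:** one interim analysis goes to the data safety monitoring board, with any others it requests. If the board advises that the arms clearly differ, the next step is described thus: "The trial steering committee can then decide whether or not to modify intake to the trial".

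**The concern.** The sentence on the first 50 participants serves two purposes. It says when the look happens, and through "Given a sample size of n = 50" it also supplies the sample on which the detectable difference is claimed. With a raw point sum and a rank test, which need equal time at risk, the natural reading is six-month scores in patients who completed six months.

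On that reading, a teenager admitted in month 2 and then withdrawn for urgent medical reasons never becomes a completer, and a replacement may be counted instead. The patients most informative about harm are those whose inclusion is not secured. Follow-up after month 6, and all follow-up of later entrants, is also unused although it is being recorded.

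On the other reading (timing only), patients with 12 months and patients with one month contribute raw sums to the same rank test.

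This is the one scheduled interim comparison in an open-label trial in teenagers whose experimental arm has fewer scheduled contacts, so its sensitivity matters.

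**Working it through.** **1. The plan's own figure.** Inputs from the section: SD 4, two-sided 5%, difference 3, n = 50 (per arm or total not stated); no power is given. SE = 4 × √(2/n per arm).

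- 50 per arm: SE = 0.80, 3/0.80 = 3.75, power = Φ(3.75 − 1.96) = 96%.
- 25 per arm (50 in total): SE = 1.13, 3/1.13 = 2.65, power = Φ(2.65 − 1.96) = 76%.

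So 3 points fits 50 per arm better, but the text does not settle it. (Separately, the section equates 3 points with one admission but scores an admission as 4; these must be reconciled.)

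**2. Follow-up at hand against follow-up used.** Inputs: 180 patients (Abstract); "Recruitment began on 6 June 2013" and completion by 30 September 2015 (Trial status), which is 27.8 months; 52 weeks of follow-up, taken as 12 months. Assumptions: even accrual, r = 180/27.8 = 6.476 per month, and no loss.

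With k trigger patients, the look falls at T = k/r + 6. Patients with full follow-up number r(T − 12) = k − 6r. The others contribute r × 12²/2 = 72r patient-months. The total is 12(k − 6r) + 72r = 12k. The six-month rule uses 6k, which is exactly half whenever T is at least 12.

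| | T (months) | Randomized | At hand | Used |
|---|---|---|---|---|
| k = 100 (50 per arm) | 21.4 | 139 of 180 (77%) | 1,200 | 600 |
| k = 50 in total | 13.7 | 89 | 600 | 300 |

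Under ramp-up, front-loaded, faster and slower accrual, and with the former target of 304 (2 × 152), the unused share runs from 48% to 56%. Part of it belongs to later entrants. Within the trigger patients alone the share beyond month 6 is 17% to 46%.

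**3. Patients left out.** Retention caps loss at 10% over 52 weeks. At a constant rate (assumed), loss by month 6 is 1 − √0.90 = 5.1%. Reaching 50 completers takes 50/0.949 = 52.7 patients (about 3 left out); reaching 100 takes 105.4 (about 5). These counts cover every loss, so urgent withdrawals are at most this many. For scale, if 3 patients with 4 points each were missing beside 50 with mean 1 (assumed), that arm's mean would rise from 1 to (50 + 12)/53 = 1.17 once they were counted.

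**4. Gain in power from all follow-up.** With 50 per arm, the six-month rule gives 25 person-years per arm (600/12/2) and all follow-up gives 50 (1,200/12/2). The admission rates are assumed, since the article gives none. The Poisson column is the exact conditional test, two-sided 5%. The last column simulates counts with gamma-distributed patient rates (frailty variance 2, assumed) and a robust rate-ratio test.

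| Admissions per year | Poisson, 25 → 50 person-years | With between-patient variation |
|---|---|---|
| 0.2 vs 0.6 | 54% → 87% | about 47% → 72% |
| 0.4 vs 0.8 | 37% → 70% | about 32% → 47% |

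**The case against.** The strongest reply is that the sentence is a timing rule. Nothing limits the data to months 0 to 6 or excludes withdrawn or later patients, and the score is described as covering deterioration over the study. The cut-off and analysis set normally sit in the monitoring board's charter, which exists and is available on request. The board may ask for any analysis, and each visit and admission is recorded as an adverse event, so a month-2 admission is on file before any withdrawal. A fixed window also has a proper reason: a raw sum compared by ranks needs equal exposure.

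Much of this stands. A reader might infer that the plan discards half the follow-up and drops withdrawn patients as a matter of fact. The article does not say so; that follows only if the trigger is also the analysis set. A reader might also infer a tilt towards showing no harm. That would require such withdrawals to be more frequent in the IBD-live arm, which no section shows; if control patients leave, the tilt reverses. The power gain depends on assumed rates, covers admissions rather than the composite, and shrinks with between-patient variation.

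What does not stand is that the timing reading removes the problem. It leaves the set undefined and makes the stated test unsuitable for unequal exposure. Board requests soften the gap but do not change the stated comparison.

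**Conclusion.** The point holds in conditional form. The interim comparison is triggered by and sized on six-month completers, its analysis set is not stated, and neither reading works well with an unadjusted sum and a rank test. On the completer reading, about 3 patients per 50 completers or 5 per 100 could go uncounted, and about half of the patient-time would be unused. The first figure rests on the 10% cap and a constant loss rate, the second on an assumed accrual pattern, though it is stable across those tried. The effect of the omitted patients on the mean score is probably small against 3 points, and its direction is unknown. The gain in power from all follow-up is material under every scenario run, from 15 to 33 percentage points, but those scenarios use admission rates and a frailty variance that the article does not supply. This is a cheap improvement to the harm comparison; it does not show that the planned look is biased.

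**What to change.** Keep the trigger and its timing, and add a few lines to the protocol and the monitoring board's charter:

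1. State whether 50 is per arm or in total.
2. Define the interim set as all patients randomized by the data cut-off, analysed as randomized. Include withdrawn and replaced patients, with events counted at least up to withdrawal.
3. Compare relapses, admissions, emergency visits and the composite score per person-time, using a rate ratio whose variance is robust to overdispersion (for example negative binomial, or Poisson with robust variance).
4. Keep the six-month Mann-Whitney comparison as supportive.

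The cost is slightly more interim programming and a model-based comparison in place of a simple rank test. No new data or patients are needed.
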